### 2.2.3 SECONDARY OUTCOMES

#### 2.2.3.1 TO DETERMINE THE EFFECT OF ARA IN PATIENTS ON MEASURES OF CARDIOVASCULAR HAEMODYNAMICS

##### Endpoints:

- (a) Change from baseline in office recorded systolic blood pressure annually (visit 7, 11) and at final visit. (variables SYSBPR and SYSBPL). Change in systolic BP is collected for right arm and left arm separately. Means of all measurements of BP (in particular measurements taken from different arms) will be calculated at each time point in accordance with NICE guidelines and these mean BP measurements will be used in the analysis. These variables are collected at each visit (see schedule of assessments in appendix III).

Rates of hypotension (<100mmHg systolic recorded in both arms or postural hypotension recorded) at any point during the study. The rates of hypotension across the study period, defined as <100mmHg systolic or >20mmHg systolic drop on standing. The outcome will be hypotension (a binary coded variable defined as hypotension at any point during the study period, coded 1, or no hypotension, coded 0).

- (b) This can be reported as two different outcomes:

- i. Hypotension (with or without symptoms) when systolic BP is <100mmHg. Specifically this variable is coded “yes” if systolic blood pressure in both arms drops below 100mmHg at any time point and “no” otherwise, i.e. {HYPO\_BP=yes IF (SYSBPR AND SYSBPL)<100mmHg} {HYPO\_BP=no IF (SYSBPR OR SYSBPL)≥100mmHg}. If this variable is coded yes at any follow up visit, then the outcome will be coded “yes”.
- ii. Postural / Orthostatic hypotension –postural or symptomatic hypotension leading to study discontinuation. If it is unclear whether the participant has symptoms it will be assumed that the participant has postural hypotension. This information regarding postural drop is recorded in the discontinuation CRF under EWDETAIL as free text and in the adverse event CRF. If postural hypotension is recorded at any time point this outcome will be coded “yes”

The variable HYPOTENSION will be derived as follows:

HYPOTENSION=1 if {(SYSBPR AND SYSBPL) < 100mmHg at ANY Visit} OR {EWDETAIL=”postural/symptomatic hypotension” at study discontinuation}

HYPOTENSION=0 if {(SYSBPR OR SYSBPL)>100mmHg at ALL Visits} AND {EWDETAIL postural/symptomatic hypotension”}

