## 2.4 SAMPLE SIZE

The estimate for the cardiovascular (CV) event rate (defined by hospitalisation for coronary heart disease, heart failure, ischemic stroke and peripheral arterial disease) and total mortality rate in patients with CKD 3b (eGFR 30-44 ml/min/1.73m^2) being 11.29 and 4.76 per 100 person years respectively gives a combined event rate of 16.05 per 100 person years. In those with eGFR in the range 45-50 ml/min/1.73m^2, the event rate is conservatively estimated to be 0.667 times as high (10.7 events per 100 person years) and we assume half the participants will fall in this range giving an overall event rate of 13.4 events per 100 person years. To detect a 20% relative risk reduction in death or cardiovascular events within 3 years in the intervention group as compared with the control group (i.e. hazard ratio=0.8) with a two sided significance of 0.05, 1455 participants per arm are required seeking 90% power and assuming 10% drop out rate per year.

We have decided to power the trial conservatively on a 20% risk reduction since this proposed treatment effect is around half the risk reduction observed in the ARA mild heart failure trial (EMPHASIS). The estimated hazard ratio in the EMPHASIS eplerenone versus placebo mild heart failure trial (only mildly symptomatic patients were included) were 0.63 (CI 0.54-0.74, p<0.001) for the composite endpoint of death from CV causes or hospitalisation for heart failure at the median follow up of 21 months. The conservative upper CI for the treatment effect was 26% reduction. The placebo CV event rate in EMPHASIS trial was similar to observational data on CV events in CKD 3b patients.

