#### 4.2.2 THE EFFECT OF ARA IN PATIENTS ON MEASURES OF CARDIOVASCULAR HAEMODYNAMICS

Office measurements of systolic blood pressure (SYSBPR) at baseline, 6 months, 1 year, 2 years and 3 years will be summarised across treatment groups using means and standard deviations. Rates of hypotension (defined in section 2.2.2.1) across the whole study period will be summarised across treatment groups using numbers and proportions of those randomised to each arm. The rates of hypotension across the study period will be analysed by log-binomial regression models and predictors will be treatment allocation and GP practice. The treatment effect will be represented as a relative risk with 95% confidence interval and associated P-value.

The mean change in systolic blood pressure each year from baseline will be analysed with a linear mixed effects model. The model will include systolic blood pressure measurement at each time point and will adjust for baseline measurement and clustering within GP practice will be accounted for as a random effect within the model. An interaction between time and randomised group will be fitted to allow estimation of treatment effect at 6 months and 1, 2 and 3 years. Although 6 months and 1, 2 and 3 years are the main time points of interest, all visits at which BP is recorded will be included in the model to aid estimation of treatment effects in the presence of missing data. The model will also include a patient specific random intercept nested within a practice specific random intercept. Results will be presented as mean difference in change from baseline in systolic blood pressure between the randomised groups at 6 months and 1, 2 and 3 years, with 95% confidence interval and associated 2-sided p value.

The model will include the following fixed effects:

- Time
- Treatment allocation
- Time×treatment allocation
- Baseline systolic blood pressure

The model will include the following random effects:

- GP practice
- Participant ID

The distribution of the change from baseline will be formally assessed for evidence of departure from normality. If necessary, data will either be transformed or analysed using a non-parametric equivalent.

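### The rule for coding HYPOTENSION as 0 does not say how missed visits count, and a higher reading of exactly 100 mmHg fits neither code

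*Combined protocol and SAP*

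**What the plan says.** SAP 2.2.3.1 describes hypotension in three ways.

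- In prose the outcome is two-valued: "a binary coded variable defined as hypotension at any point during the study period, coded 1, or no hypotension, coded 0".
- The blood pressure component, HYPO_BP, is yes if "systolic blood pressure in both arms drops below 100mmHg at any time point and “no” otherwise". Its formula for the negative is "no IF (SYSBPR OR SYSBPL)≥100mmHg".
- The combined variable has two lines. The first is "HYPOTENSION=1 if {(SYSBPR AND SYSBPL) < 100mmHg at ANY Visit", with postural or symptomatic hypotension on the discontinuation form (EWDETAIL) as an alternative route to 1. The second is "HYPOTENSION=0 if {(SYSBPR OR SYSBPL)>100mmHg at ALL Visits", joined to a condition on EWDETAIL. The operator in that condition is not legible in the copy read, and nothing here depends on it.

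SAP 4.2.2 says that hypotension "will be summarised across treatment groups using numbers and proportions of those randomised to each arm". It then plans a log-binomial model for the relative risk, with treatment and practice as predictors. SAP 4.2.1 and 4.3 place secondary outcomes in the intention-to-treat population. SAP 2.1 schedules 15 follow-up visits over 156 weeks.

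**The concern.** The two lines treat missing visits differently. One low visit is enough for a 1, whatever else is missing. A 0 asks for a reading above 100 mmHg at all visits, and the plan does not say whether that means all scheduled or all attended visits. If a programmer takes it as scheduled, a participant with normal readings who misses one visit, withdraws or dies is neither 1 nor 0. A log-binomial model drops that record unless told otherwise. Only non-events are lost in this way.

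Two things would follow. The modelled risk would be too high. And if visits were missed more often in one arm, that difference would appear as a difference in hypotension. Hypotension is a named secondary safety outcome with its own relative risk and P-value.

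The cut-offs raise a separate problem that needs no missing data: 1 requires both arms below 100 mmHg, and 0 requires at least one arm above it.

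**Working it through.** The plan states no hypotension rate, relative risk or attendance by arm, so there is no figure of its own to reproduce.

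**Inputs from the documents**

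- Follow-up visits: five up to week 26, then (156 − 26)/13 = 10 more, so 15. This matches V15 in the schedule.
- Attrition: protocol 12.3 assumes 10%, so 90% are retained. SAP 2.4 gives its figure as "assuming 10% drop out rate per year", so 0.9³ = 72.9% are retained at three years. The two documents differ, so both are used.

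**Assumptions**

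- p, the share with a recorded event, is 5%.
- c is the share of non-events with all 15 visits. Retention alone gives c = 0.90 or 0.729. Missed visits lower it further: at 2% missed per visit 0.98¹⁵ = 0.739, and at 5% 0.95¹⁵ = 0.463.

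**Modelled risk if incomplete non-events have no value**

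Risk = p / [p + (1 − p)c]

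| c | Calculation | Modelled risk | Ratio to 5% |
|---|---|---|---|
| 0.90 | 0.05 / (0.05 + 0.95 × 0.90) | 5.5% | 1.10 |
| 0.729 | 0.05 / (0.05 + 0.95 × 0.729) | 6.7% | 1.35 |
| 0.463 | 0.05 / (0.05 + 0.95 × 0.463) | 10.2% | 2.04 |

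**Relative risk when the true risk is 5% in both arms**

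| Completeness, spironolactone v control | Modelled risks | Relative risk |
|---|---|---|
| Equal, any value | equal | 1.00 |
| 0.80 v 0.90 | 6.17% v 5.52% | 1.12 |
| 0.729 v 0.90 | 6.73% v 5.52% | 1.22 |

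For 0.729 v 0.90, a true risk anywhere from 2% to 20% gives 1.23 down to 1.18.

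**Simulation.** The formula treats every event as seen, but drop-out also hides events. A simulation with 300,000 per arm, 15 visits, constant risk per visit totalling 5%, exponential drop-out and random missed visits allows for this.

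| Drop-out over 3 years and missed visits, spironolactone v control | 0 needs all scheduled visits | 0 needs one recorded reading |
|---|---|---|
| 10% and 2% in both | 6.9% in both, RR 1.00 | 4.7% in both, RR 1.00 |
| 27.1% and 2% v 10% and 2% | 7.8% v 6.9%, RR 1.13 | 4.3% v 4.7%, RR 0.92 |
| 20% and 5% v 10% and 2% | 10.9% v 6.8%, RR 1.60 | 4.4% v 4.6%, RR 0.94 |

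The last column shows that recoding removes the inflation but not all bias. Shorter follow-up leaves fewer chances to record an event.

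**Denominators.** The summary in SAP 4.2.2 divides by all randomised. An unassigned 0 does not change its numerator or denominator, so that percentage is not inflated. Under the scheduled-visits reading it does rest on a different population from the model.

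**Exactly 100 mmHg.** Take a participant whose higher reading at one visit is 100 mmHg, with all other visits above 100 and no postural record. The =1 line fails because both arms are not below 100. The =0 line fails because neither arm is above 100 at that visit. HYPO_BP codes the same visit as no, because it uses at or above 100.

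**The case against.** The best defence is that the =0 line is simply the =1 line negated. Both-below at any visit becomes at-least-one-not-below at all visits, so AND/OR and any/all flip as a negation requires. On that view it means everyone else, and visits with no reading are ignored. The two-valued prose, the default of no in HYPO_BP and the intention-to-treat population all support this, and it is probably what was intended.

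That stands as a reason not to call the loss of participants certain. It does not settle the wording, because the same SAP writes the missing-data rule where it wants one. In SAP 2.2.3.4 a participant needs only one recorded potassium value to be classed as not hyperkalaemic. The no-event code for the primary outcome in SAP 4.1.1 is limited explicitly to non-missing items. The provision for secondary outcomes in SAP 4.4 relies on mixed models over repeated time points, which does not cover an ever/never outcome in a log-binomial model. The negation argument also fails at 100 mmHg, since the opposite of below 100 is at or above 100.

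It is fair to add that SAP 4.7 treats secondary outcomes as exploratory, which limits the weight of the point.

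A reader might go further and infer that the relative risk is in fact biased, because only one arm can stop a drug and Supplementary Table 2 puts 331 of 677 against 576 of 695 in the on-treatment set. The documents do not support that. Those counts describe adherence, and protocol 9.8 and 12.4 continue follow-up after treatment is stopped. The post hoc row excluding peripheral arterial disease gives 1679.5/661 = 2.54 v 1786.5/687 = 2.60 years per person at risk, a gap of about 2%. That time ends at the primary event, so it is only a rough guide to attendance. As an illustration, completeness of 70% v 72% at 5% risk gives a relative risk of 0.0699/0.0681, about 1.03.

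**Conclusion.** The derivation needs correcting, on two grounds of different strength.

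- **Certain under either reading:** a visit whose higher reading is exactly 100 mmHg prevents a 0 without giving a 1. This contradicts both HYPO_BP and the two-valued definition in the same section.
- **Conditional on reading the line as all scheduled visits:** incomplete non-events leave the model and recorded events stay. At 5% risk the modelled risk is overstated about 1.10 times with 90% completeness and 1.35 times with 72.9%, and by more if visits are also missed. The relative risk is biased if completeness differs between arms. It stays at 1.00 with equal completeness and no true effect.

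The sizes rest on an assumed risk and on planning figures for attrition. Completeness by arm is not in the documents, so neither the size nor the direction of any actual bias can be stated. It would also be wrong to conclude that the published percentage is inflated, because the planned summary divides by all randomised.

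**What to change.** Keep the =1 line and apply it first. Replace the =0 line in SAP 2.2.3.1 with:

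> HYPOTENSION=0 if the participant does not meet the =1 rule (including EWDETAIL), at least one post-randomisation blood pressure is recorded, and at every visit with a recorded blood pressure at least one arm is ≥100 mmHg. Missing only if the =1 rule is not met and no post-randomisation blood pressure is recorded.

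Applying the =1 line first matters. Postural cases come from the discontinuation form, so a rule based only on readings could code such a case as both 1 and 0, or as both 1 and missing. The ≥100 cut-off is the SAP's own, from HYPO_BP. The SAP should also say how a visit counts when only one arm was measured and it is below 100 mmHg, because that visit would otherwise meet neither line.

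In SAP 4.2.2, use this same denominator for the summary percentage and the model, and report the number in the model. If the analysis has been run, state which reading the code used. Optionally, add first hypotension per person-year of blood pressure follow-up, since recoding does not remove all bias from unequal follow-up.

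The cost is a few lines of wording and code. No new data are needed.

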#### 2.2.3.2 TO DETERMINE THE EFFECT OF ARA IN PATIENTS ON DECLINE IN RENAL FUNCTION

##### Endpoint:

Change in Albumin Creatinine Ratio (ACR) (variable ALBCREAT). The percentage change in albumin creatinine ratio from baseline will be computed at 3 years. An increase in ACR level indicates worsening of renal disease. Numbers and percentages with a ≥30% increase in creatinine will be reported.

Change in Estimated Glomerular Filtration Rate (eGFR) (variable GFR). The percentage change from baseline in eGFR from baseline will be computed at 6 months, 1, 2 and 3 years. A reduction in eGFR indicates worsening of renal disease. Numbers and percentages with a drop of  $\geq 25\%$  in eGFR from baseline and  $\geq 20\%$  drop in eGFR from previously reported will also be presented.

#### 2.2.3.3 TO DETERMINE THE TREATMENT COSTS AND BENEFITS.

This objective will form part of the health economic analysis and will be described in a separate health economic analysis plan.

#### 2.2.3.4 TO DETERMINE THE SAFETY OF ARA IN PATIENTS WITH STAGE 3b CKD

##### Endpoints:

- (a) Rates of adverse events. All adverse events are recorded in the AE report CRF. The number of participants experiencing at least one AE and the number of AEs per participant will be reported. Number of SAEs will also be reported. Rates of hyperkalaemia:
- (b) Hyperkalaemia is defined as a potassium level  $\geq 5.5\text{mmol/l}$ . Potassium [K] is recorded at each visit. A binary variable will be derived as experiencing hyperkalaemia at any time point. Hyperkalaemia will be recorded as “yes” if the participant has potassium levels  $\geq 5.5\text{mmol/l}$  at any point during the study and “no” if at least one potassium measure is recorded and it does not meet the definition of hyperkalaemia. If a participant has hyperkalaemia at any point during the study, the maximum value of Hyperkalaemia for that patients will be used to derive a second variable to indicate whether the maximum hyperkalaemia was mild ( $5.5\text{-}5.9\text{mmol/l}$ ), moderate ( $6.0\text{-}6.4\text{mmol/l}$ ) or severe ( $>6.5\text{mmol/l}$ ).

#### 2.2.4 SECONDARY OUTCOMES- INTENSIVELY PHENOTYPED SUBGROUP

No patients were recruited to the intensively phenotyped group therefore objective 7 cannot be addressed.

#### 2.2.5 SAFETY OUTCOMES

All adverse events during the first 6 months of follow-up including rates of hyperkalaemia will be recorded for the analysis of the safety profile of spironolactone in CKD. Following this initial 6 month period, **only the following AEs will be monitored by the member** of the Research Team performing that visit. Safety concerns (i.e. significant decrease in eGFR (20% between visits, or 25% from baseline), rise in potassium levels (to above 5.5), and drop in BP (to below 100 in both arms)).

### 2.3 TARGET POPULATION

Eligible patients, from 120 practices recruited by 6 NIHR School for Primary Care Research departments, with previously recorded blood test results suggesting CKD stage 3b will be invited to take part in the trial.

### 2.3.1 INCLUSION CRITERIA

Participants must fulfil either of the **Search 1** or **Search 2** criteria and all of the following:

#### **Search 1**

Evidence of stage 3b CKD using the MDRD equation. This includes patients on the CKD register undergoing annual monitoring who have had two or more recent blood samples in the 30-50 ml/min/1.73m^2 range in the preceding 24 months, with a minimum of 6 weeks between tests.

- Where only one test has been performed in the preceding 24 months and is in the 3b range, the patient will be invited to attend the baseline visit at least 6 weeks from the initial test, the eGFR result from this can be taken as the second confirmatory test. Physicians will also be reminded that standard care suggests a second confirmatory test.

#### **Search 2**

- Patients with eGFR results in the preceding 24 months with a reading of 25-29 ml/min/1.73m^2
- Participant is willing and able to give informed consent for participation in the study.
- Male or Female, aged 18 years or above.
- Able (in the recruiting physician's opinion) and willing to comply with all study requirements.
- Willing to allow his or her General Practitioner and consultant, if appropriate, to be notified of participation in the study.
- Willing to provide contact details to the Research Team (encompassing recruitment centre and practice staff), for use at any time should the need arise, on trial related matters.
- If the participant is a female of child-bearing potential, they are willing to ensure effective contraception during the trial period.

### 2.3.2 EXCLUSION CRITERIA

The participant may not enter the study if ANY of the following apply:

- Female participants who is pregnant, lactating or planning pregnancy during the course of the study.
- Type 1 diabetes mellitus
- Terminal disease or felt otherwise unsuitable by their physician.
- Chronic heart failure clinical diagnosis or known LVSD with EF<40%.
- Recent myocardial infarction (within 6 months).
- Active cancer with less than 1 year life expectancy or in palliative care.
- Alcohol or drug abuse.
  - Suspected or known current hazardous or harmful drinking, as defined by an alcohol intake of greater than 42 units every week.
  - Suspected or known current substance misuse.
- Most recent potassium result >5.5 mmol/L, where not thought to be spurious, or previous raised potassium needing a reduced dose of ACEI/ARB or intolerance to spironolactone.
- eGFR >60 ml/min/1.73m^2 in the last 6 months and no identifiable reason for a temporary reduction in eGFR.

- Serum potassium at baseline over 5 mmol/L.
- Documented Addisonian crisis and/or on fludrocortisone.
- Documented symptomatic hypotension or baseline systolic blood pressure under 100mmHg.
- Recent acute kidney injury or admission for renal failure.
- ACR > 70 mg/mmol.
- Prescription of medications with known harmful interactions with spironolactone as documented in the British National Formulary including tacrolimus, lithium and cyclosporine.
- Any other significant disease or disorder which, in the opinion of the recruiting physician, may either put the participants at risk because of participation in the study, or may influence the result of the study, or the participant's ability to participate in the study.

## 2.4 SAMPLE SIZE

The estimate for the cardiovascular (CV) event rate (defined by hospitalisation for coronary heart disease, heart failure, ischemic stroke and peripheral arterial disease) and total mortality rate in patients with CKD 3b (eGFR 30-44 ml/min/1.73m^2) being 11.29 and 4.76 per 100 person years respectively gives a combined event rate of 16.05 per 100 person years. In those with eGFR in the range 45-50 ml/min/1.73m^2, the event rate is conservatively estimated to be 0.667 times as high (10.7 events per 100 person years) and we assume half the participants will fall in this range giving an overall event rate of 13.4 events per 100 person years. To detect a 20% relative risk reduction in death or cardiovascular events within 3 years in the intervention group as compared with the control group (i.e. hazard ratio=0.8) with a two sided significance of 0.05, 1455 participants per arm are required seeking 90% power and assuming 10% drop out rate per year.

We have decided to power the trial conservatively on a 20% risk reduction since this proposed treatment effect is around half the risk reduction observed in the ARA mild heart failure trial (EMPHASIS). The estimated hazard ratio in the EMPHASIS eplerenone versus placebo mild heart failure trial (only mildly symptomatic patients were included) were 0.63 (CI 0.54-0.74, p<0.001) for the composite endpoint of death from CV causes or hospitalisation for heart failure at the median follow up of 21 months. The conservative upper CI for the treatment effect was 26% reduction. The placebo CV event rate in EMPHASIS trial was similar to observational data on CV events in CKD 3b patients.

## 2.5 RANDOMISATION AND BLINDING IN THE ANALYSIS STAGE

Randomisation was carried out using Sortition with block randomisation with randomly varying block size. The randomisation was stratified by practice to ensure balance of the two arms within each practice. .

BARACK D is a PROBE trial where neither the patients nor physicians are blinded to the trial treatment but the primary endpoints will be assessed by an independent endpoint committee who are blinded to the treatment arm. The trial statisticians will not be blinded to the treatment allocation.

